#### Treatment as Usual (TAU)

TAU will be the standard care available in the local community, which will be determined by the needs of each family and the local service provision. The first line of services is provided at the primary care level by universally available professionals such as GPs, health visitors and midwives. For individuals who require more support after birth the help they can receive will vary depending on where they live and the degree of their needs. In general, TAU is often a package of support from family support workers, enhanced health visiting, social worker or midwifery services (listening visits), one-to-one support from clinical psychologists (provided through local CAMHS services), psychotherapists or counsellors, postnatal support groups, crèches providing respite, parenting education workshops, peer-supported groups, home-visiting services, child psychiatry and family therapy. The Service Users and Support (SUS) questionnaire will be used to check what usual care services both groups of participants receive during the trial.

### Intervention fidelity

Adherence to the MTB intervention protocol will be achieved in close collaboration with the Yale team (including the primary developers) in the following ways:All participant contact will be guided by the written intervention manual as well as other training materialsAll clinicians will receive extensive training in the MTB model via in-person, taped, or videoconference training sessions led by the Yale MTB trainers. The Yale MTB trainers include senior nurse and mental health supervisors and home visitorsAll MTB practitioners will record detailed information regarding their direct and indirect contact with familiesIn order to ensure that home visits adhere to the Yale MTB intervention programme after each visit practitioners will complete a Home Visit Form. This aims to describe the visits in detail and compare them with the US MTB intervention home visits. In particular practitioners record the length, nature and focus of the visit and the families’ level of engagement. It also summarises the focus of the visit, e.g. parenting, health, mental health, etc., and the time spent on each topicSpecially trained supervisors will undertake model fidelity monitoring by random sampling of families at each site and discussing the outcomes with the relevant sites at compliance visitsAll practitioners receive regular supervision by Yale-trained local UK supervisors. These specially trained supervisors meet monthly via phone with the Yale MTB trainersRegular disciplinary and interdisciplinary supervision will be provided by specially trained supervisors and the Yale MTB team (in addition to supervision provided as usual by the practitioners’ line managers)

### Participant retention

Dropping out of treatment is common in prevention studies in the perinatal period [73]. In one of the key studies of the NFP programme, active refusals to participate in the trial ran at approximately 20 % (with a further 20 % passively dropping out by not responding to mailed invitations to participate), which is higher than the estimates from the Yale pilot study [23]. However, it is notable that a much smaller proportion refused to participate in the research evaluation once they had agreed to randomisation (3.8 %). From the outset of the FNP study to the 2-year outcome phase a further 21 % were lost to follow-up. In the UK, the FNP programme had an initial uptake rate of 83 % of eligible families and a later dropout rate of 15 %. We thus aim to over-recruit by 15 % to take attrition into account, leading to an initial intake target of *N* = 240, so that 100 per arm is achieved at the year-2 outcome point. An overview of participant timeline is presented in Table 2.

**Table 2 Tab2:** Time requirement per participant

		Study period				
			Post allocation			
Time point	Prebaseline	Baseline	6 months	Year 1	18 months	Year 2
Recruitment:						
Eligibility screen	X					
Informed consent	X					
Allocation		X				
Research assessment:						
Questionnaires		X	X	X	X	X
Reflective Functioning				X		
Maternal sensitivity				X		X
Developmental assessment						X
Attachment classification				X		X
Overall time involvement	15 min	1 h	15 min	2 h	15 min	2 h

### Data management

The data will be collected by experienced RAs who have been trained to work with high-risk populations. Necessary safeguarding policies will be in place to ensure the safety of the RA collecting the data. In particular, contact information of the assessment location will be left with another member of staff before leaving for the assessment. Regular contact with the RA will be maintained at the start and end of the assessment. In situations where an RA feels to be in immediate danger they will be instructed to follow safeguarding policies to call the police.

Regular supervision with the trial management team, the coordinator and the principal investigators will ensure the reliability of data collection. Where necessary the RAs will be fully trained and certified in administering and coding research measures.

All coding will be supervised by the principal investigators. Where standardised coding measures are required the RAs will undertake full training courses and complete necessary reliability checks. The data will be coded by an RA who does not know the family and will be blind to the subject status (intervention or control). Interrater reliability will be established for all instruments.

Every week, questionnaire data collected the previous week will be coded, verified and double-entered directly into secure web databases. Audio interviews will be transcribed and video-taped material downloaded, any personal identifiable information will be removed and the data stored on a secure server ready for coding. To check the reliability of the process, 10 % of the records will be randomly selected and will be reviewed, coded and entered independently by RAs for calculation of interrater agreement rates. The databases will be compared and checked for errors before transferring to an SPSS (v. 21.0) file for analysis.

### Data transfer

In the study, all participant data as outlined previously in this protocol will be collected in accordance with the participant Consent Form and Participant Information Sheet. All participant data will be appropriately sent to [name] for statistical analysis and UCL will act as the data controller of such data for the study. [name] will be responsible for the processing, storage and disposal of all participant data in accordance with all applicable legal and regulatory requirements, including the Data Protection Act 1998 and any amendments thereto.

Data will be stored on a secure server dedicated exclusively to this project that has encrypted access. Only the research team will have access to the data and to information identifying participants. Research data and personally identifying data will be stored in separate, web-accessible, secure databases. All research data will be stored in locked filing cabinets in each site. Similarly, Consent Forms will be stored separately from the research data in locked filing cabinets in each site. Risks to subject confidentiality will be minimised by adopting suitable data storage procedures in accordance with best practice guidelines and in accordance with the Data Protection Act. Subjects will be assigned ID numbers. The master ID list that links subject names with ID numbers will be kept on a highly secure password-protected server. All information concerning allocation to condition (TAU or MTB) will be held securely by the randomisation centre. Clinical records and other relevant clinical information regarding participants in the MTB arm will be held by the NSPCC, following their standard governance protocols.

### Data analysis

The primary outcome, maternal sensitivity, is an average of several ordinal scores and is typically found to be approximately normally distributed. The primary analysis will be a regression analysis testing group differences in mean sensitivity at year 1 after adjustment for baseline characteristics. Clustering by therapist and site will be allowed for by computing robust standard errors [74]. Continuously distributed secondary outcomes will be treated in the same manner. The risk of child protection intervention will be described using the Kaplan-Meier method and summarised by the proportions of children with child protection intervention over 2 years period of observation. The primary analysis for this outcome will be Cox regression, adjusting for key baseline characteristics.

Where there are missing data, these will be evaluated either by multiple imputation or a sensitivity analysis determined by the pattern of missing data. In doing so, we will follow the procedures and guidance outlined by Sterne and colleagues [75]. Mediational analyses of change mechanisms (e.g. age 12 months’ maternal sensitivity-mediating treatment effects on attachment at age 2 years) will be tested using bootstrap methods described by MacKinnon and Dwyer [76] and Preacher and Hayes [77].

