
This randomised clinical trial will test the hypothesis that an intensive home-visiting programme focussed on promoting young parents’ sensitive attunement to their infants and their ability to mentalise on their baby’s thoughts, feelings and needs, will lead to improvements in the sensitivity of parenting of children age 2 years compared to parents who receive routine care. The study will also examine several secondary hypotheses, including that the programme will increase offspring rates of secure attachment, improve cognitive and behavioural outcomes and promote maternal mental health.

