### Outcome measures

#### Primary outcome

The primary outcome is the quality of parenting, operationalised as maternal sensitivity [26]. Maternal sensitivity will be measured at ages 1 and 2 years and will be treated as a continuous score, with both time points included in the primary analysis.

In order to measure parenting sensitivity at ages 1 and 2 years, we will use several short tasks from our existing studies of attachment and another ongoing clinical trial. The first task focusses on mother-infant interaction in the context of free-play. Known as the ‘three-boxes procedure’, the mother shows the child experimenter-provided toys in three containers in a set order [35–37]. The second is a procedure pioneered by Smith and Pederson [36]. In this task, mother and infant are left to explore a relatively empty room, while the mother must also complete a distraction questionnaire. Another task involves brief observations, one focussing on book-sharing and the other on a difficult-to-manipulate toy. Finally, we are using a separate joint book-reading observation in which the content of the book involves strong attachment-related scenarios. In each case, maternal sensitivity will be rated, using Emotional Availability Scales [38], an observation tool. The scales describe and assess four dimensions on the adult side (sensitivity, structuring, nonintrusiveness and nonhostility) and two dimensions on the child side (responsiveness and involvement with the caregiver). Dimensions are measured on a scale, with scores of between 1 and 7. Scales will be standardised and summed to yield a total score across all tasks for the main analysis. The use of specific contexts for mother-infant interactions will also allow us to determine whether the intervention is changing the particular processes associated with each domain of child development in tertiary analyses.

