### Sample size

A minimum of 200 participants (100 in each arm) will enter into the evaluation. The sample size calculation is motivated by the effect size estimates on the primary outcome (maternal sensitivity) and the attachment outcome at 1 year.

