#### Power analysis

We based our power analyses on previous interventions aimed at improving parenting sensitivity. The overall meta-analytic average for sensitivity-focussed intervention trials in Bakermans-Kranenburg’s (2003) review was *d* = .44 which is equivalent to a correlation of *r* = .22. If we assume four covariates and a single df test of treatment effect, with a reduced model R^2^ of .15 and a full model R^2^ of .20, then 129 participants would be required for 80 % power at alpha = .05. Bakermans-Kranenburg further reported that the meta-analytic average of randomised studies was *d* = .36 (*r* = .18), which for the equivalent analysis and power would require a sample size of 190. We also computed power to detect effects on attachment security. We estimated the effect size based on meta-analytic data, based on the assumption that the MTB intervention would be effective in enhancing parental sensitivity: such studies yield average effect sizes of *d* = .45 in the aforementioned meta-analysis [70] and hence the power for this outcome would be equivalent or greater to that for sensitivity.

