### Data monitoring

#### Data monitoring

The Trial Steering Committee (TSC) will take the role of monitoring trial safety and data monitoring. The statistician will review the data on an ongoing basis, including any adverse event records, and report this to the TSC. Detailed reports will be prepared by the TSC statistician to monitor safety/adverse event data, recruitment and dropout rates. The formal statistical interim analysis of the primary outcome will be reported to the TSC after the end of the first outcome phase.

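### The primary analysis is defined on both years in one section and on year 1 only in another, and a year-1 test cannot address the stated hypothesis about children aged 2

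*Protocol article*

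**What the plan says.** All statements are in the current text of the protocol article.

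- **Overview and rationale (Background).** The trial hypothesis is that the programme "will lead to improvements in the sensitivity of parenting of children age 2 years compared to parents who receive routine care".
- **Primary outcome (Methods).** Sensitivity is measured at ages 1 and 2, "with both time points included in the primary analysis". Table 1 likewise lists year 1 and year 2 for this outcome.
- **Data analysis.** "The primary analysis will be a regression analysis testing group differences in mean sensitivity at year 1 after adjustment for baseline characteristics". Standard errors are to be robust to clustering by therapist and site.
- **Sample size.** "The sample size calculation is motivated by the effect size estimates on the primary outcome (maternal sensitivity) and the attachment outcome at 1 year". The closing time reference may belong to attachment alone or to both outcomes.
- **Power analysis.** One single-df test of treatment at alpha .05, with no year named.
- **Participant retention.** Intake is raised to 240 "so that 100 per arm is achieved at the year-2 outcome point".
- **Data monitoring.** "The formal statistical interim analysis of the primary outcome will be reported to the TSC after the end of the first outcome phase". The phase is not tied to a year by name.

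**The concern.** A confirmatory trial needs one primary test, fixed in advance. Here two Methods sections define the primary analysis differently, and the narrower of the two leaves out the age at which the hypothesis is stated. An analysis plan can follow one of these sections but not both.

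The choice matters because the answers can differ. An effect present at year 1 that fades by year 2, or one that appears only at year 2, would be a success under one rule and a failure under another. Even with the same true effect in both years, sampling error alone will often put one year above the significance threshold and the other below it.

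Timing adds to the exposure. The Abstract places outcome assessments around the first and second birthdays, so the natural reading of the first outcome phase is year 1. On that reading the interim analysis and the primary analysis in Data analysis use the same data. The result goes to a Trial Steering Committee whose membership includes researchers. The meaning of the primary outcome could then be settled with comparative results already known.

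**Working it through.** **1. Do the passages reconcile?**

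| Section | Time point implied |
|---|---|
| Overview and rationale (hypothesis) | age 2 |
| Primary outcome, Table 1 | years 1 and 2 |
| Data analysis | year 1 |
| Sample size | ambiguous; year 1 at most |
| Power analysis | none named |
| Participant retention | 100 per arm retained to year 2 |
| Data monitoring | first outcome phase, probably year 1 |

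Primary outcome and Data analysis both speak of the primary analysis and are incompatible. The hypothesis fits a reading that includes year 2, but not a year-1 regression. No section ranks the time points or divides alpha.

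**2. Does the sample size settle it?** The plan's inputs are four covariates, one treatment df, reduced R² .15, full R² .20, alpha .05 and 80% power.

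- f² = (.20 − .15)/(1 − .20) = .0625. With a noncentral F on 1 and N − 6 df and noncentrality f²N, the smallest N is 128. The plan gives 129.
- For d = .36 (r = .18) no R² is given. Scaling the increment gives .05 × (.18/.22)² = .0335. With full R² held at .20, f² = .0335/.80 = .0418 and N = 190. The plan gives 190.

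The arithmetic reproduces. It is for one test at one unspecified time, so it would serve year 1 or year 2 equally and does not decide between them.

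**3. False-positive rate if the choice stays open.** The between-year correlation ρ of the test statistics is not in the document. I take .3, .5 and .7.

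- Either year may be called primary: 1 − P(|Z₁| < 1.96 and |Z₂| < 1.96) = 9.5%, 9.1%, 8.3%.
- The two-year average may be chosen too (simulation, 2,000,000 draws): 10.5%, 9.7%, 8.6%.

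**4. How often would the two single-year tests disagree?** Assume true d = .36 in both years, 100 per arm and no covariates.

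- Expected z in each year = .36 × √(100/2) = 2.546.
- P(significant in a given year) = P(Z > 1.960 − 2.546) = 72.1%.
- P(significant in both years) = 55.6%, 58.3%, 61.5% for ρ = .3, .5, .7.
- P(exactly one significant) = 2 × (72.1% − P(both)) = 33%, 28%, 21%.

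**5. What does each candidate contrast cost in power?** Same basis. The two-year average has expected z = 2.546/√((1 + ρ)/2) = 3.157, 2.939, 2.761, so power is 88%, 84%, 79%, against 72% for one year. If the effect were present in one year only, the average would carry half the mean effect. Expected z would be 1.579, 1.470, 1.381 and power 35%, 31%, 28%. Covariate adjustment raises the single-year power to roughly 78 to 82%, depending on how R² is scaled. Under equal effects it does not change the ordering.

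**The case against.** The best defence is that only two sections actually specify the primary analysis. The hypothesis is a Background statement, and it is compatible with an analysis that includes year 2. On that view Data analysis is simply the outlier and the reader can tell what was meant. This narrows the conflict but does not remove it: Data analysis is where the test is specified, and it names year 1.

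Three stronger readings are tempting and are not supported.

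- *Year 2 is already the primary time point because intake was sized for it.* Keeping 100 per arm to the last visit is an attrition allowance. It is compatible with a year-1, year-2 or combined analysis.
- *The trial will run at 8 to 10% type I error.* That holds only if the investigators may test each option and then choose. No section proposes this. The figure measures what the open wording would permit.
- *Year 1 is a low-exposure test.* The first birthday is half-way through the postnatal period, but visits are weekly before it and fortnightly after it. About 52 of 78 scheduled postnatal visits (52 + 26), or 67%, fall in the first year.

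It is also fair to say that which contrast to prefer is a design choice for the sponsor. That stands, and the fix allows for it.

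**Conclusion.** The point holds. The current text gives incompatible definitions of the primary analysis, and the one in Data analysis cannot test the stated hypothesis. This is a contradiction within the article, not detail deferred to an analysis plan. The sample size calculation is not at fault.

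The size depends on assumptions. The false-positive rate of about 8 to 10% (9 to 11% with the average as a third option) assumes correlations of .7 to .3 and free choice after testing. The 21 to 33% disagreement assumes d = .36 in both years, 100 per arm and no covariates. The concern that the choice could follow sight of the data rests on the first outcome phase being year 1, which the schedule suggests but the text does not state.

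It should be corrected before the analysis, because it leaves the trial's single confirmatory claim undefined.

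**What to change.** Replace the year-1 sentence in Data analysis with one repeated-measures linear model of the year-1 and year-2 sensitivity scores. Its terms are arm, time, arm-by-time and the minimisation factors (site, maternal age group, baseline EPDS group). Keep the stated robust standard errors for therapist and site clustering.

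Name one primary contrast at two-sided .05. The MTB minus TAU difference at year 2 matches the hypothesis as written. If the sponsor prefers the two-year average, the hypothesis must be reworded to match. Report the remaining contrasts as secondary.

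Then align five places: the hypothesis in Overview and rationale, Primary outcome, the time reference in Sample size, Data analysis, and Data monitoring. The last should say which year and which contrast the interim examines, and what role that result has. Fix all of this before any comparative year-1 result is seen.

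The change is wording in the protocol and analysis plan, plus the formal amendment that the protocol requires for any modification. It needs no new data. The cost is that the year-1 result becomes secondary. A year-2 contrast also has less power than the two-year average if effects are equal in both years (72% against 79 to 88% on the unadjusted basis above). The average, in turn, loses heavily if the effect is confined to one year.

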### Minding the Baby®: an interdisciplinary approach

The home-visiting intervention programmes presented above have mostly focussed on either the practical aspects of parenting or the quality of the mother-child relationship and attachment. MTB aims to address both these elements of parenting.

The UK MTB clinical team includes two qualified practitioners: a nurse or health visitor and a social worker who are both highly trained and supervised in particular techniques and developmental approaches tailored for working with vulnerable young mothers. The nurse provides advanced levels of practical parenting support including individual and family health assessments, nutritional advice and family planning. The social worker provides mental health support to mother and baby, in-home assessment and intervention for mild to moderate mental health problems like depression, anxiety and PTSD symptoms that the mother might be affected by. Crucial to the success of the MTB programme is the mother’s relationship with the MTB practitioners. Their engagement and fostering of ongoing relationships with these at-risk, first-time young mothers, as well as having the professional expertise that matches their complex health, social and mental health needs, is aimed to diminish attrition from the programme. This kind of integrative model is considered to be crucial for maximising both parental and child outcomes across a range of domains.

Following the Yale model, the UK MTB is grounded in well-established developmental research, builds on the experience of similar successful programmes, is a relationship-based model, delivers a flexible model of care design to match the varying and often complex needs of at-risk families, and has a robust, manualised system of training and supervision.

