## Methods

### Design

This is a multisite randomised controlled trial, with randomisation at the case level. This trial will utilise a two-arm design, with random allocation to either MTB plus Treatment as Usual (TAU) or a TAU-only control condition. Allocation will be by minimisation, controlling for maternal age, maternal depression and study site. Figure 1 shows a flow diagram of the study design, and the Standard Protocol Items: Interventions for Reporting Trials (SPIRIT) checklist is presented in Additional file 1 [33, 34].

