### Recruitment

Recruitment will take place at three UK sites: York, Sheffield and Glasgow. Participants in York and Sheffield will be screened if they live within a defined geographical area around each site of approximately 15 miles of the city centre (the precise geographical boundaries will vary in each site).

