### Randomisation

Eligible consenting participants will be randomised on a 1:1 basis by the randomisation centre (supervised by [name]) at a separate site, who will manage randomisation. Monitoring of data quality and integrity will be done separately by [name], study statistician. Together they will act as DMEC and will have power to break confidential ID codes should ethical concerns arise. A computer-generated adaptive minimisation algorithm [72] that incorporates a random element will be used with the following balancing factors: treatment centre, maternal age (below 20 versus 20 years or older) and current depressive symptomatology (< 10 versus ≥ 10 on the EPDS). These minimisation factors have been selected because previous research has shown that these factors are associated with poorer outcomes on some of our dependent measures or are highly plausible treatment modifiers. Once a family has been approached and has consented to take part, anonymised screening data will be sent to the randomisation centre by the trial coordinator. The randomisation centre will send the results of the randomisation to the local clinical manager within 72 h, ensuring that the research team is fully blind to the condition that the family is allocated to. Participants will be informed about their group allocation, as blinding to a psychosocial treatment of this nature is not possible. The outcome assessors will be blind to the participants’ allocation. During training, all research assistants (RAs) will be briefed regarding the importance of blindness to condition and they will record any instances where the participating family discloses its condition inadvertently, so that the impact of this can be examined in the data analysis. Coding of the primary outcome will be done independently from video recordings by raters who have no contact with the participants.

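### Robust standard errors clustered by site rest on three clusters, so the primary test loses either its error rate or its power; the effect of therapist clustering depends on an unstated number of practitioner pairs

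*Protocol article*

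**What the plan says.** The Data analysis section of the Protocol article defines the primary test: "The primary analysis will be a regression analysis testing group differences in mean sensitivity at year 1 after adjustment for baseline characteristics". It continues: "Clustering by therapist and site will be allowed for by computing robust standard errors". Continuous secondary outcomes are to be handled the same way. The section gives no cluster unit for TAU mothers, no small-sample correction and no reference distribution.

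Four other places bear on this:

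- **Recruitment:** "Recruitment will take place at three UK sites: York, Sheffield and Glasgow".
- **Design:** the trial is multisite "with randomisation at the case level", and "Allocation will be by minimisation, controlling for maternal age, maternal depression and study site". The Randomisation section also lists treatment centre as a balancing factor.
- **Minding the Baby®: an interdisciplinary approach:** "The UK MTB clinical team includes two qualified practitioners". Planned intervention adds that the two practitioners alternate their visits. The number of teams, overall or per site, is not stated.
- **Sample size:** "A minimum of 200 participants (100 in each arm) will enter into the evaluation".

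**The concern.** A cluster-robust (sandwich) variance estimates the standard error from the spread of cluster contributions, and its justification needs many clusters. Clustered by site, it has three.

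Site is also the wrong kind of factor for this treatment. Both arms are present in every site and allocation is balanced within site, so site acts as a stratum, which a fixed effect handles directly.

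Therapist clustering is a different problem. It exists only in the MTB arm. Because two practitioners alternate, the natural unit is the pair and not the single therapist. The text does not say what cluster a TAU mother belongs to.

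At stake are the p-value and confidence interval of the primary result and of every continuous secondary outcome.

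**Working it through.** **Inputs from the Protocol article.** Three sites (Recruitment). N = 200, 100 per arm (Sample size). Alpha .05, 80% power, R² from .15 to .20 with four covariates, and a second effect of r = .18, d = .36 (Power analysis).

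**Assumptions, because the article is silent.** Two-sided test; 3, 6 or 12 practitioner pairs in total (1, 2 or 4 per site); therapist ICC from 0 to .10.

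**Step 1: the plan's own figure.** f² = (.20 − .15)/(1 − .20) = .0625. With a noncentral F test on 1 and N − 6 degrees of freedom and noncentrality f²N, 80% power is reached at N = 128; the article states 129, so it reproduces. For r = .18, f² = .0324/(1 − .1824) = .0396 and N = 201, against 190 stated. Nothing below depends on the 190. At N = 200, ordinary power is 80% for f² = .0396 and 94% for f² = .0625.

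**Step 2: type I error with site as the cluster.** With G equal sites and 1:1 allocation within each, the estimate is the mean of G site differences. The sandwich standard error with the G/(G − 1) factor is the usual standard error of that mean, so the statistic follows t on G − 1 = 2 degrees of freedom. For 2 df, P(|t| > c) = 1 − c/√(2 + c²).

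- Normal reference, with the factor: c = 1.96, so 1 − 1.96/√5.8416 = 18.9%.
- Normal reference, without the factor: c = 1.96 × √(2/3) = 1.600, so 1 − 1.600/√4.561 = 25%.
- t(2) reference: 5% by construction.

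Simulation with the factor and a normal reference gave 18–20%, and 19–21% with sites of 40, 80 and 80.

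**Step 3: power if t(2) is used.** The critical value is 4.303 and the noncentrality is √(200 f²).

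- f² = .0396: noncentrality 2.815, power 35% (against 80%).
- f² = .0625: noncentrality 3.536, power 48% (against 94%).

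**Step 4: type I error with the MTB practitioner pair as the cluster.** TAU mothers are singletons, the reference is normal, the G/(G − 1) factor is applied, and there are 4,000 null trials per cell.

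| Pairs | Site terms in model, ICC 0 to .05 | No site terms, ICC .05 |
|---|---|---|
| 3 | 12–21% | 12–14% |
| 6 | 9–10% | 7–9% |
| 12 | 6–7% | about 6% |

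At ICC .10 with 3 pairs and site terms the figure is about 26%.

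**Step 5: what ordinary standard errors would do.** With site fixed effects and no therapist effect, ordinary errors hold 5%. With a therapist effect and 3 pairs, the model variance is about 1/100 + 1/100 = .02, while the true variance is about .02 + ICC/3. At ICC .05 the ratio is .03667/.02 = 1.833, the effective cut-off is 1.96/√1.833 = 1.448, and type I error is about 15%. At ICC .02 it is about 9%, and at ICC .10 about 23%. Ignoring therapists is therefore not safe if the result is to apply beyond the practitioners in the trial.

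**The case against.** The strongest reply is that one sentence in an article does not fix an implementation. It names no reference distribution or small-sample correction, and such details are commonly left to an analysis plan, which is not shown. A reader might infer that the primary test will have a type I error near 20%. The document does not support that: the figure needs site as the cluster with a normal reference, or about three pairs with a non-zero ICC and site terms. This stands. It does not rescue site-level clustering, because the alternative reference gives up most of the power that the sample size was meant to buy.

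The sentence can also be read as therapist within site, with the sandwich at therapist level. That is a fair reading. The result then turns on the number of pairs. A reader might take it as given that there are few, but the article describes a two-person team and not how many teams exist. With 12 pairs the inflation is small.

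A reader might also infer that site has been left out of the model. The text does not show this. The baseline characteristics are not listed, and four covariates would fit age, depression and two site indicators. Site terms alone would not, however, repair a sandwich clustered on three sites.

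Finally, TAU mothers can be treated as singletons and the pair as the unit, so a workable therapist definition exists. It only needs to be stated.

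**Conclusion.** The concern holds in conditional form. The stated method names site as a clustering level and there are three sites. On that reading, the test either rejects a true null about 19% of the time (25% without the correction factor), or holds 5% with power of about 35% at d = .36 and 48% at the larger planning effect. This needs no assumption about therapists; the closed form assumes equal sites and balanced arms, and unequal sites changed it little.

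On the therapist reading, the size is uncertain because the number of pairs and the ICC are not given. It ranges from slight (6–7% with 12 pairs) to serious (up to 21% with 3 pairs at ICC .05), with site terms and a normal reference. The documents do not support a flat statement that the primary p-value will be wrong or that robust standard errors are invalid in every form. They do support changing the method for site, and stating the unit and small-sample method for therapist.

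**What to change.** 1. Remove site from the robust-variance clustering. Enter site, maternal age group and baseline depression group as fixed effects in the primary model and in the continuous secondary models.
2. Handle therapist clustering in the MTB arm only, with the practitioner pair as the unit and TAU mothers as singletons. Use either a partially nested random effect with Kenward-Roger or Satterthwaite degrees of freedom, or a bias-reduced sandwich with Satterthwaite degrees of freedom. Name one of these as primary.
3. State the number of pairs per site. If each site has only one, the therapist effect cannot be separated from the site-by-treatment interaction. In that case report the site-fixed-effects result with model-based errors, say that it is conditional on the practitioners in the trial (type I error about 15% at ICC .05 if generalised beyond them), and show it over a stated ICC range.

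The cost is a change of wording and a slightly more complex model, settled before unblinded analysis; no new data are needed. Intervals will be somewhat wider than from a naive regression, and therapist-level inference will have low power if pairs are few. The small-sample behaviour of the two methods in item 2 was not simulated here and should be checked once the number of pairs is known.
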